### Statistical Analysis

The DACIMA Clinical Suite platform enables the collection of web-based data and their extraction in SAS (SAS Institute) or SPSS (IBM Corp) format. The statistical analysis is exploratory, involving the calculation of 95% CI. The data will be described for the whole analyzed population. Continuous variables will be described by mean and SD or median and IQR. Categorical variables will be described by the size and frequency of every modality. Mean comparison will be performed by analysis of variance or by nonparametric tests if the hypothesis of normality is rejected.

The normality of continuous variables will be verified with the Shapiro-Wilk test. The statistical tests are bilateral with a 95% CI. A chi-square test will be performed for categorical variables. Yates correction or the Fisher exact test will be used if the conditions of validity for the chi-square test are not met.

A multivariate analysis will be performed with each complication as a dependent factor. The independent variables will be age, gender, ethnic specificity, BMI, CIED type, procedure type, procedure priority, implantation center (private and public), and CIED implanting operator whether he is an electrophysiologist or not (interventional cardiologist or cardiac surgeon).

Univariate logistic regression will be carried out with a 10% output threshold. The final model will be performed with the parameters selected by the backward stepwise method of Wald. The selected variables in the final model will be tested at the 5% threshold. The interaction between selected parameters is tested at the 10% threshold. The intermediate analyses will be carried out after formulating the statistical analysis plan.

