## Results

In total, 27 investigators, comprising 14 from the public sector and 13 from the private sector, volunteered to take part in the study. It is worth noting that some of the investigators were involved in both the public and private sectors. A total of 1500 consecutive patients were enrolled for a 12-month follow-up period following CIED implantation. Sixty percent (n=900) of the patients were from the public sector, while 40% (n=600) were from the private sector. The patients’ mean age was 70.1 (SD 15.2) years, with a sex ratio of 1:15. A total of 1298 (86.3%) patients received a conventional PM and 75 (5%) patients received a biventricular pacemaker (CRT-P). ICDs were implanted in 127 (8.5%) patients. Of these patients, 45 (3%) underwent CRT-D implantation. The detailed analyses of this study are currently under investigation and will be published elsewhere in the near future.

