### Study Limitations

This study presents some limitations that must be considered in the interpretation of the results. This study is voluntary for both investigators and patients, and there is no routine audit to monitor the proportion of enrolled patients by participating electrophysiologists or cardiologists. This currently limits our ability to examine exact implant rates and to examine equity of access to PM therapy across the country. Some patients were lost to follow-up.

We identified all complications documented in patients during hospitalization and follow-up. We believe that this approach is the most accurate and comprehensive way to detect complications. In addition, this study was not designed to assess the effects of each investigator’s experience level and the volume of procedures performed individually. Therefore, the electrophysiologists’ or interventional cardiologists’ positions on their learning curve may influence the rate of complications mainly in teaching hospitals.

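### The stated tests of operator type, and to a lesser degree of public/private sector, make no allowance for clustering of 1500 patients within about 27 investigators, so their standard errors are too small if operators differ

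*Protocol article*

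**What the plan says.** The Statistical Analysis section of the protocol article names the tests (chi-square, with Yates correction or Fisher's exact test as fallback) and a regression for each complication with nine independent variables. Two of the nine describe the provider: "implantation center (private and public" and "CIED implanting operator whether he is an electrophysiologist or not (interventional cardiologist or cardiac surgeon".

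The selection path is also fixed. First, "Univariate logistic regression will be carried out with a 10% output threshold". Then, "The final model will be performed with the parameters selected by the backward stepwise method of Wald". Finally, "The selected variables in the final model will be tested at the 5% threshold". On sidedness: "The statistical tests are bilateral with a 95% CI". The section calls the analysis exploratory. It names no random effect, GEE, robust variance, or operator or centre term.

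The Results section reports 1500 patients from 27 investigators (14 public, 13 private), with 900 patients in the public and 600 in the private sector. It adds that "some of the investigators were involved in both the public and private sectors". Study Limitations says that operators' "positions on their learning curve may influence the rate of complications mainly in teaching hospitals", and that the study was not designed to assess individual experience or volume.

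**The concern.** A Wald or chi-square test at patient level assumes independent patients. For a covariate that is constant within an operator, what matters is how many operators stand on each side of the comparison. If complication rates vary between operators for reasons other than operator type, patients of one operator resemble each other, and the patient-level standard error is too small. The article allows for such variation through the learning curve, leaves it unmodelled, and still tests an operator-level predictor.

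Predictors of complications are part of the main objective in Outcomes. The Discussion hopes the study's information will help develop a national peri-implantation management protocol. A spurious finding that one kind of operator or one sector has more complications would be a misleading input. The same problem affects the 10% screen, which decides what enters the model, and the confidence interval for the overall complication rate.

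**Working it through.** The article gives no sample-size, power or precision figure to reproduce. Its only nominal figures are the 5% and 10% thresholds, which the formula below returns exactly at ICC = 0.

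**Inputs from the article.** 1500 patients; 27 investigators; two-sided tests at 5% (final model) and 10% (screen); cited overall pacemaker complication rates of 4% to 10% (Discussion).

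**Assumptions, none given in the article.** The 27 investigators approximate the implanting operators; the ICC; the spread of caseloads (coefficient of variation, CV); in the simulation, 13 of 27 operators are electrophysiologists.

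**Formulas**, for a covariate constant within operator:
- mean caseload m = 1500/27 = 55.6
- design effect DE = 1 + ((1 + CV²)·m − 1)·ICC
- actual error = 2·(1 − Φ(z/√DE)), with z = 1.96 for the 5% test

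Example, equal caseloads (CV = 0), ICC 0.01: DE = 1 + 54.6 × 0.01 = 1.55; √DE = 1.24; 1.96/1.24 = 1.58; error 11.5%; effective sample 1500/1.55, about 971.

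| Assumed ICC | DE (equal caseloads) | SE multiplier | Effective N | Error, equal caseloads | Error, CV 0.7 |
|---|---|---|---|---|---|
| 0.001 | 1.05 | 1.03 | 1422 | 5.6% | 6.0% |
| 0.005 | 1.27 | 1.13 | 1179 | 8.2% | 9.9% |
| 0.01 | 1.55 | 1.24 | 971 | 11.5% | 14.6% |
| 0.02 | 2.09 | 1.45 | 717 | 17.5% | 22.7% |
| 0.05 | 3.73 | 1.93 | 402 | 31.0% | 38.5% |

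With equal caseloads the error is 5.6/5 = 1.1 to 31.0/5 = 6.2 times nominal. At the 10% screen it is 18.6% at ICC 0.01 and 25.5% at ICC 0.02. A threefold error at the 5% level needs an ICC of about 0.016 (equal caseloads) or 0.010 (CV 0.7).

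**Simulation check.** 27 operators, 1500 patients, caseload CV 0.7, a random operator intercept on the logit scale, no true effect, 1500 replicates per setting. Error of the ordinary Wald test of operator type:

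| Complication rate | Operator SD 0.3 | Operator SD 0.5 |
|---|---|---|
| 1% | 3.0% | 4.3% |
| 2% | 7.1% | 9.1% |
| 5% | 9.9% | 16.8% |
| 10% | 11.9% | 24.3% |

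The inflation shrinks for rare outcomes because the same logit-scale SD implies a smaller ICC on the observed scale: at SD 0.5, about 0.003 at a 1% rate and 0.025 at 10%. At 1% (15 expected events) the Wald test is also conservative to begin with: 2.9% with no operator variation. With a larger SD of 0.7, the error at 1% and 2% was 9.1% and 15.0%.

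**Sector**, at SD 0.5 and a 5% complication rate: 16.7% if no operator works in both sectors, 12.6% if 8 do, 10.2% if 16 do, 5.5% if all 27 do.

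**After correction.** A cluster-robust standard error with a t reference on 24 df gave about 4% to 10% across settings. Where operators differed a lot the gain was large: 38.5% fell to 9.5% for operator type at SD 0.7 and a 10% rate. Where they hardly differed there was none: 7.1% against 8.5% at SD 0.3 and a 2% rate.

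**The case against.** The article is a condensed document and refers to a statistical analysis plan that is not shown; that plan could add a random effect or robust variance. The analysis is labelled exploratory, and operator experience is disclosed as a limitation. All this is true, but the article does not merely stay silent on method. It fixes the tests, the covariates, the selection rule and the thresholds, and that described model does not give valid standard errors for operator type if operators differ. An exploratory label does not make the promised 95% intervals correct.

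Other objections stand and limit the size of the point:
- A reader might infer that false predictors are several times too likely throughout. The documents give no ICC, and at 0.001 to 0.005 with equal caseloads the factor is only 1.1 to 1.6. The plan models each complication separately, and these are rarer than the overall rate.
- A reader might treat sector like operator type. Some investigators worked in both sectors, so sector varies within operator, and the design-effect formula overstates its inflation.
- The 27 are investigators, not necessarily operators. Statistical Analysis counts cardiac surgeons among the operators, whereas the Discussion describes the 27 as electrophysiologists and interventional cardiologists.
- The learning-curve remark says that rates may differ, not that they do.
- Nothing in the article ranks operator type or sector as its most policy-relevant result. The other seven predictors were not examined here.

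**Conclusion.** The point holds in a limited form. As described, the analysis ignores clustering while testing one covariate that is fixed within operator and another that is partly so. The direction is clear if operators differ: standard errors too small, most of all for operator type. The size is unknown. It is about 6% to 31% for a nominal 5% test of operator type, given an ICC of 0.001 to 0.05, equal caseloads and 27 operators. It is higher with unequal caseloads, slight or absent for single complications at 1% to 2% if operator variation is modest, and smaller for sector the more operators span both sectors. This should be fixed before operator or sector effects are published, but the documents do not support calling the predictor analysis as a whole invalid.

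**What to change.** Fit the predictor models with a random intercept for implanting operator (or site). Alternatively, use GEE or cluster-robust standard errors with a small-sample correction and a t reference based on the number of clusters. Code sector per procedure, not per investigator. Use the same approach in place of unadjusted chi-square tests for operator type and sector, at the 10% screen, and for the confidence interval of the overall complication rate. Report the number of implanting operators, how many worked in both sectors, and the estimated between-operator variance.

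The Results section says the detailed analyses are still in progress, so this is a change of analysis wording, provided the database identifies the operator or site. The costs are wider intervals for operator type and sector, and a correction that is still approximate with about 27 clusters (simulated error of the robust test about 4% to 10%). Random-intercept models for the rarest complications were not tested here, and operator effects on those outcomes are best reported with caution.

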### Timeline

Patient enrollment and data collection began on January 18, 2021, and continued until February 18, 2022. Follow-up continued until all patients had 1-year data. The end of the study was therefore scheduled for February 18, 2023 (Figure 1).

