**Figure 1 figure1:**
[figure not shown]
The Timeline of the Nature CIED study.

If patients missed a scheduled follow-up visit, they or their relatives were contacted by phone to assess any adverse event and to reschedule a follow-up appointment.

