### Outcomes

The main objective of this observational study is to assess the incidence, characteristics, and predictors of major and minor complications arising in the initial 12 months following the implantation of CIEDs.

The complications were characterized as major when life-threatening or requiring surgical reintervention for correction, and minor when suitable for treatment on an outpatient basis, involving device reprogramming, or requiring exclusive clinical observation [11]. Major complications include implantation failure, lead-related reinterventions, tamponade or myocardial perforation, pneumothorax requiring drainage, hematoma requiring evacuation, wound or pocket infection, systemic infections or endocarditis, Twiddler syndrome, and procedure-related deaths. Minor complications include pacing threshold increase, phrenic nerve stimulation, heart failure or left ventricular ejection fraction decrease, pericardial effusion, and conservatively treated hematoma and pneumothorax.

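### Twelve-month complications are analysed by simple frequencies and logistic regression although some patients were lost to follow-up, so incidence depends on how early leavers are coded and odds ratios may be distorted

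*Protocol article*

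**What the plan says.** The Outcomes section sets the main objective: to "assess the incidence, characteristics, and predictors of major and minor complications arising in the initial 12 months following the implantation of CIEDs". Procedure-related deaths count as a major complication; other deaths are not an outcome.

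For the analysis, the Statistical Analysis section describes categorical variables by counts and frequencies. For predictors it says "A multivariate analysis will be performed with each complication as a dependent factor" and names one type of regression: "Univariate logistic regression will be carried out with a 10% output threshold", followed by backward Wald selection and a 5% test in the final model. It names no method that uses follow-up time, censoring or competing events.

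On completeness, Study Limitations says "Some patients were lost to follow-up", without number or timing. The Timeline section says "Follow-up continued until all patients had 1-year data" and derives the study end date from it. For missed visits, the text under Figure 1 says that "they or their relatives were contacted by phone to assess any adverse event" and, in the same sentence, that a new appointment was to be arranged.

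**The concern.** A logistic model for a 12-month outcome needs each patient's status at 12 months. For someone who had no complication and was last seen in month 3, that status is unknown. A plain yes/no analysis must leave the patient out or enter a no. Leaving out keeps everyone with an early event but removes event-free leavers, so incidence rises. Entering a no assumes that nothing happened in the unobserved months, so incidence falls.

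The incidence is half of the main objective, so the headline figure would depend partly on a coding choice. The other half, the predictors, is at risk only if loss is related to a predictor (sector or age, for example) or to the complication itself.

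A related problem concerns outcomes that need a device check or an echocardiogram, such as a raised pacing threshold or a fall in ejection fraction. A telephone call cannot reveal them. Where a missed visit was never made up, the patient's status for these outcomes is unknown from that point.

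**Working it through.** The article gives no loss rate, death count, event timing or expected complication rate for this study, so there is no stated figure to reproduce. The following is an illustration under stated assumptions.

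**Inputs.** N = 1500 (Results). Assumed true 12-month risk 8%, inside the 4%-10% that the Discussion cites for pacemakers. Assumed timing: 4% early, 4% spread evenly over the rest of the year. Assumed: a fraction c is lost evenly over the year, after the early events and independently of complications, so on average half of the late risk is observed in those lost (4% + 2% = 6%).

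**Incidence.**
- Leavers coded no: (1 − c) × 0.08 + c × 0.06.
- Event-free leavers dropped: the value above divided by [that value + (1 − c) × 0.92].

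| c | Coded no | Dropped |
|---|---|---|
| 5% | 0.076 + 0.003 = 0.079 | 0.079 / (0.079 + 0.874) = 0.083 |
| 15% | 0.068 + 0.009 = 0.077 | 0.077 / (0.077 + 0.782) = 0.090 |
| 20% | 0.064 + 0.012 = 0.076 | 0.076 / (0.076 + 0.736) = 0.094 |

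For scale, the 95% CI half-width at 8% is 1.96 × √(0.08 × 0.92 / 1500) = 0.014, or 1.4 points. At 15% loss the error is 0.3 point (coded no) or 1.0 point (dropped); at 5% it is 0.1 or 0.3 point.

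**Odds ratio, true value 1.0, loss differing between two groups.**
- Dropped, 15% v 5%: (0.077/0.782) / (0.079/0.874) = 1.09.
- Dropped, 20% v 5%: (0.076/0.736) / (0.079/0.874) = 1.14.
- Coded no, 15% v 5%: (0.077/0.923) / (0.079/0.921) = 0.97.
- Coded no, 20% v 5%: (0.076/0.924) / (0.079/0.921) = 0.96.

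Sampling error for a sector comparison (900 v 600 patients, 8% in each, so 72 and 48 events): the SE of the log odds ratio is √(1/72 + 1/828 + 1/48 + 1/552) = 0.194, giving a 95% CI around 1.0 of about 0.68 to 1.46.

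**Second check.** A hazard model was run with true risk p of 4% or 10%, cumulative complication hazard −ln(1 − p), and 1/12, 50% or 75% of that hazard in month 1. Exit had a constant monthly hazard −ln(1 − c)/12, independent of complications.
- At 5% exit, the relative error in incidence is −0.6% to −2.5% (coded no) and +2.4% to +4.4% (dropped).
- At 20% exit, it is −3.2% to −10.3% and +10.9% to +19.9%. The largest absolute error is 11.85% − 10% = 1.85 points, against a CI half-width of 1.5 points at 10%.
- With 10% exit in both groups, a true odds ratio of 2.111 is estimated as 2.106 to 2.112.
- With 20% v 5% exit in either direction, a true odds ratio of 1.00 becomes 0.92 to 1.09 (coded no) or 0.87 to 1.16 (dropped).

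**The case against.** The strongest reply has five parts.

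- **Handling of incomplete patients may be in the SAP, which is not shown.** This stands for missing-data rules, and their absence is not the point. The point is the model that the article does fix, set against the loss that it admits.
- **Several complications are perioperative, and the analysis is called exploratory.** For implantation failure, tamponade, pneumothorax and similar events, logistic regression is defensible. That argues for keeping it there, not for using it alone over a year. The article itself promises medium-term results.
- **Coding a patient who dies of another cause as never having had a complication is not an error.** This is correct: it is what a cumulative incidence with death as a competing event estimates. The calculation above therefore applies to loss to follow-up, not to deaths.
- **The distortion is small beside sampling error.** This is so at 5% loss or less. Odds ratios are almost unchanged when loss is equal across groups, and even unequal loss shifts them by less than the width of the interval. At 20% loss with exclusion, however, the error in incidence can exceed the CI half-width.
- **Missed visits had a remedy.** A reader might infer that they were covered only by telephone and that such patients were counted as free of device-detected complications. The documents support neither: the same sentence provides for a new appointment, and no counting rule is given.

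A reader might also take the Timeline sentence as a report that every patient completed a year. It can fairly be read as explaining the calendar end date, so the wording is loose rather than a proven false claim.

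**Conclusion.** The concern holds in limited form. The article sets a 12-month incidence and its predictors as the main objective, names only methods that need a known 12-month status, and admits that some patients do not have one. The incidence estimate then moves up or down with the coding: 9.0% or 7.7% for a true 8% at 15% loss, and 8.3% or 7.9% at 5%. Odds ratios are at risk only if loss differs by predictor or is related to the complication.

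These figures rest on assumed risk, timing and loss, and on loss being independent of complications; dependent loss could make the error larger. A reader might infer that the results are biased, or that every predictor will show a spurious association. The documents do not support that: they give no loss rate, no death count and no coding rule, so the most that can be said is that the results may be biased, in a direction set by the coding.

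**What to change.** 1. Estimate 12-month incidence by the Aalen-Johansen cumulative incidence function, censoring at last contact and treating death not related to the procedure as a competing event.
2. Use cause-specific Cox (or Fine-Gray) models for predictors of complications arising during follow-up. Keep logistic regression for perioperative complications.
3. For complications detectable only by device check or echocardiography, censor at the last in-person assessment when a missed visit was not made up.
4. Reword the Timeline sentence to agree with Study Limitations, and report how many patients completed 12 months.

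Cost: analysis wording and slightly more complex reporting. The Results section says that detailed analyses are still under way, so the change is possible. The case report form was completed at each scheduled visit, so last-contact dates should largely exist, but the article does not confirm that onset dates were recorded. The onset of device-detected events is known only to the interval between visits at 1, 3, 6 and 12 months. Censoring also assumes that those lost resemble those who stayed, which should be stated.

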### Expected Implications

NATURE-CIED is the first national and North African study that will (1) provide validated data on short- and medium-term complications and their predictors, which will allow us to individualize high-risk patients for optimal care, (2) identify the epidemiologic and demographic characteristics of Tunisian patients undergoing CIED implantation, and (3) clarify the contemporary CIED indications in Tunisia and their compliance with international guidelines.

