**Conclusions:**

This study will establish the most extensive contemporary longitudinal cohort of patients undergoing CIED implantation in Tunisia, presenting a significant opportunity for real-world clinical epidemiology. It will address a crucial gap in the management of patients during the perioperative phase and follow-up, enabling the identification of individuals at particularly high risk of complications for optimal care.

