### Conclusions

NATURE-CIED study will fill an important gap in the management of patients undergoing CIED implantation both perioperatively and during follow-up and will identify patients at particularly high risk of complications for optimal management.

In Tunisia, this study will yield the largest contemporary longitudinal cohort of patients undergoing CIED implantation and will provide real-world data regarding heart rhythm diseases’ epidemiology and management with insights into the degree of adherence to international guidelines.

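### The article promises to identify individual high-risk patients, but its stated exploratory analysis selects and tests predictors in the same 1500 patients and does not show that such patients can be recognised

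*Protocol article*

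**What the plan says.** The promise appears three times in the Protocol article, each time unconditionally:

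- Methods, Expected Implications: "which will allow us to individualize high-risk patients for optimal care".
- Abstract, Conclusions: "enabling the identification of individuals at particularly high risk of complications for optimal care".
- Discussion, Conclusions: the study "will identify patients at particularly high risk of complications for optimal management".

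The analysis meant to support it is in Methods, Statistical Analysis:

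- "The statistical analysis is exploratory, involving the calculation of 95% CI".
- "A multivariate analysis will be performed with each complication as a dependent factor".
- Nine candidate predictors are listed, beginning "The independent variables will be age, gender, ethnic specificity, BMI, CIED type, procedure type, procedure priority, implantation center (private and public" and ending with whether the operator is an electrophysiologist.
- There is a univariate logistic screen at 10%, backward stepwise Wald selection, and then "The selected variables in the final model will be tested at the 5% threshold". Interactions among the selected variables are tested at 10%.

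One cohort serves every step: "A total of 1500 consecutive patients were enrolled for a 12-month follow-up period following CIED implantation". The section describes no second sample. Study Limitations does not mention the issue.

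**The concern.** The claim and the analysis answer different questions. The stated procedure produces a list of variables associated with a complication. Saying that individual patients at particularly high risk will be identified is a claim about prediction: that the variables, taken together, separate patients who will have a complication from those who will not, well enough to act on.

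Two gaps follow. A variable can be clearly significant and still separate patients poorly. And when variables are kept because they looked strong in a data set, their coefficients in that data set are too large on average, so any grading of patients built on them looks sharper than it will prove in new patients.

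At stake is the article's closing message. Discussion, Summary expects the study's information to help develop a national peri-implantation protocol, so readers may take the list of predictors as a working tool for picking out patients.

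**Working it through.** The article gives no predictive-accuracy, event-count or sample-size calculation, so there is no figure to reproduce.

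**1. Claim against analysis.** The three claim sentences speak of recognising high-risk patients. The steps stated for the analysis are screen, select, test and test interactions. None of them yields a patient's predicted risk or a measure of how well risk is separated. Expected Implications does call its data validated, but this matches the checking of recorded data described under Data Sources, not validation of a model.

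**2. Does a significant predictor identify patients?** Take one binary predictor with assumed prevalence 40%, odds ratio 1.8 and average risk 7%. The average lies within the 4% to 10% that Discussion, Summary cites for pacemakers; prevalence and odds ratio are illustrative.

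- Solve 0.6·p0 + 0.4·p1 = 0.07 with p1/(1−p1) = 1.8·p0/(1−p0). This gives p0 = 5.4% and p1 = 9.4% (unrounded 0.0543 and 0.0936).
- Share of events among patients not flagged: 0.6 × 0.0543 / 0.07 = 47%.
- Flagged patients without a complication: 1 − 0.0936 = 91%.
- Sensitivity = 0.4 × 0.0936 / 0.07 = 0.535. False-positive fraction = 0.4 × 0.9064 / 0.93 = 0.390. So c = 0.5 + (0.535 − 0.390)/2 = 0.57.

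This holds however many events are observed, so it is not a sparse-data problem.

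**3. How far does same-data selection overstate?** The stated rule was simulated without the interaction step: n = 1500, 300 cohorts per scenario, performance checked in 40,000 new simulated patients. The nine variables become 12 parameters if device type has four levels and procedure type three. Device mix follows Results: 1298, 75, 127 − 45 = 82, and 45 of 1500. The other inputs, apart from the 60% public share, are assumed. True effects were modest (c about 0.60). Values are for cohorts that kept at least one predictor.

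| Event rate | Events (1500 × rate) | Events per parameter (÷ 12) | c, same patients | c, new patients | Median calibration slope |
|---|---|---|---|---|---|
| 1% | 15 | 1.25 | 0.66 | 0.53 | 0.22 |
| 3% | 45 | 3.75 | 0.62 | 0.53 | 0.31 |
| 5% | 75 | 6.25 | 0.60 | 0.54 | 0.41 |
| 10% | 150 | 12.5 | 0.60 | 0.55 | 0.53 |

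The cited rates of 3% to 10% cover all complications together, so the 1% row stands for a single complication, which is what the stated models take as outcome.

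Further runs under other assumed effects:

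- Weak effects, 4% to 10% events: c 0.58–0.60 in the same patients against about 0.53 in new ones; slope 0.26–0.39.
- Stronger effects, 4% to 10% events: c 0.65–0.66 against 0.58–0.61; slope 0.51–0.73.
- True c about 0.70, 10% events: c 0.70 against 0.67; slope 0.81.

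The direction is the same in every run. At 4% to 10% events the slope ranges from roughly 0.3 to 0.8.

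**4. What the slope means for the plan's own output.** The slope is the average factor by which the fitted log odds ratios should be multiplied to fit new patients. As a rough guide, a reported odds ratio of 1.8 (ln 1.8 = 0.588) corresponds to exp(0.3 × 0.588) = 1.19 at slope 0.3, and to exp(0.8 × 0.588) = 1.60 at slope 0.8.

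**The case against.** The strongest reply is that this argues from silence. Data Sources and Statistical Analysis both mention a statistical analysis plan, and measures of discrimination, calibration and internal validation commonly belong there. That stands in part. A reader might infer that no validation will ever be done; the article does not show that. What remains does not depend on silence: the article fixes the selection procedure down to its thresholds, labels the work exploratory, and still states the conclusion unconditionally.

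Second, the stated aims (Study Aims; Outcomes) are incidence, characteristics and predictors, not a prediction model. Discussion, Summary is hedged, saying that predictors may identify such patients. This also stands. A reader might infer that the study fails a primary objective of prediction, but no such objective is set. The fault lies in the implication and conclusion sentences. Reading individualize as singling out risk groups does not remove it: the abstract speaks of individuals, and risk groups need the same evidence of separation.

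Third, the plan names no c-statistic, so a reader who inferred that an inflated c will be published would go beyond the document. In the weak-effect runs the same-data c is also close to the best attainable one. The overstatement that applies to the plan as written is in the odds ratios, which is why the slope is the better summary.

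Fourth, the size rests on assumed effects and covariates, and a pooled outcome is not what Statistical Analysis specifies. That is correct, and it is why only a range is given.

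**Conclusion.** The concern holds in limited form. Three sentences promise, without condition, to identify high-risk individuals. The stated exploratory analysis selects and tests predictors in one cohort of 1500. This overstates the effects of those kept and does not show that high-risk patients can be recognised.

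The direction is secure; the size is not. At event rates of 4% to 10%, simulated slopes of roughly 0.3 to 0.8 depend on the assumed true effects, the assumed covariate mix (beyond what Results gives) and omission of the interaction step. Stronger true effects and more events shrink the optimism, but it was present in every scenario examined.

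Two stronger readings should be avoided. The selected predictors are not said to form the national protocol: Discussion, Summary says only that the study's information will be valuable in developing one. Nor do the documents fix any particular amount of optimism.

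**What to change.** Restate the conclusion in Abstract (Conclusions), Expected Implications and Discussion (Conclusions) as *factors associated with complications (exploratory)*.

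If the high-risk claim is to be kept, add to Statistical Analysis, for the major-complication outcome defined under Outcomes:

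1. a predicted 12-month risk for each patient;
2. a c-statistic and calibration slope, both corrected for optimism by a bootstrap that repeats the entire screening and selection procedure in each resample;
3. a sentence making the high-risk statement depend on those results.

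The number of bootstrap samples, any shrinkage of coefficients and any grouping of predicted risk can be left to the trial statistician.

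The cost is wording alone for the first route, or a little more programming for the second, with no new data. Results says the detailed analyses are still in progress, so either route is open. The drawback is that reported performance will look less favourable.
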